**Methods and analysis:**

In this multimodal neuroimaging randomized trial, a total of 96 female MWoA participants and 30 female healthy controls (HCs) will be recruited. The 96 female MWoA participants will be randomized into three groups: Group A (CAT group), Group B [ipsilateral acupuncture (IAT) group], and Group C (sham CAT group) in a 1:1:1 allocation ratio. Each group will receive 30 min of treatment every other day, three times a week, for 8 weeks, followed by an 8-week follow-up period. The primary outcome is the intensity of the migraine attack. Data will be collected at baseline (week 0), at the end of the 8-week treatment period (weeks 1–8), and during the 8-week follow-up (weeks 9–16). Adverse events will be recorded. Multimodal MRI scans will be conducted at baseline and after 8-week treatment.

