### Sample size calculation

Regarding the sample size calculation for the modulation of brain functional networks by acupuncture, there is no established method. However, in line with the requirements of brain functional network analysis techniques (Bossier et al., 2020), a sample size of 30 cases per group should provide relatively stable reproducibility. We plan to include 30 cases in each treatment group, and with an estimated loss rate of 8%, we will aim for 32 cases per group, resulting in a total of 96 cases. The HCs group will consist of 30 cases, as they are undergoing examinations only once and are generally not participants in loss.

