### Seed-based FC analysis

The seed-based FC analysis will include all MWoA and HC participants and who completed the entire trial. PAG plays a pivotal role in the context of acupuncture for migraine treatment, so the PAG was chosen as the ROI for FC analysis. The location of the PAG seed will be selected based on previous studies (MNI coordinates: 0, −32, −12; size: 6 mm radius sphere) (Kucyi et al., 2013; Coulombe et al., 2017). The time course of each voxel in PAG will be extracted and averaged. Pearson correlation coefficients will be calculated between the average time series of PAG and each voxel throughout the whole brain. The obtained correlation coefficients will undergo Fisher-Z-transformed to increase normality. A clusterwise family-wise error rate (FWE) correction will also be considered.

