### Clinical data analysis

Statistical analysis will be performed by independent statisticians who will have no knowledge of group allocation or the intervention process. Clinical outcomes will be analyzed using SPSS 28.0 statistical software (SPSS Inc., Chicago, IL, USA). All statistical analyses will adhere to the intention-to-treat principles. The missing data of participants who drop out will be handled using multiple imputation by chained equations (Azur et al., 2011), which can impute mixtures of continuous, binary, unordered categorical, and ordered categorical data. In addition, a per-protocol population analysis will be performed on participants who have completed at least 80 percent of their treatment protocol after randomization. Qualitative data will be presented as percentages [*n* (%)] and compared using the Chi-square (χ^2^) test. Quantitative data will be reported as means ± SDs and IQRs. Shapiro–Wilk tests will be performed to assess the normality of the data. Comparisons among the three groups will be analyzed using one-way analysis of variance (ANOVA), and non-parametric tests will be employed when the distribution is not normal. Outcomes will be analyzed using a one-way repeated measures ANOVA to evaluate the impact of time, group, and time × group interactions on migraine attacks. Comparisons of categorical data among groups will be examined using χ^2^ tests or Mann–Whitney U tests. All hypothesis tests will be two-tailed analyses, with statistical significance determined by a *p*-value < 0.05.

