### Neuroimaging data analysis

The structural MRI data will be analyzed using the VBM toolbox within SPM12. The steps will include interlaminar time difference correction, spatial difference correction, head motion correction, normalization, and Gaussian smoothing (Yao et al., 2021). During head motion correction, images of participants with translations of less than 1 mm and rotational movements of less than 2° will be involved in the subsequent analysis. The MRI data will be analyzed using PANDA, GRETNA and BrainNet Viewer toolboxes and SurfStat. In VBM analysis, generalized linear regression model analysis will be used and between-group VBM comparisons will be made using corrected subject migraine attack intensity, migraine attack frequency, etc. (control covariates: age, PSQI, SAS, SDS, etc.) and total intracranial volume by two-sample *t*-test. A significant difference between groups will be indicated when *p* < 0.05 (FWE corrected). Only collections with more than 20 voxels will be considered as statistically significant brain regions. First, the FC of PAG in the baseline session will be compared between the migraine patients and normal participants using two sample *t*-test with FWE correction. Second, two-factor three-level mixed design ANOVA (Time: baseline and after treatment; Treatment: CAT, IAT, and sham CAT) will be conducted on migraine patients to explore the effect of treatment schedule on the FC of PAG after FWE correction. *Post hoc* analysis will be implemented using paired *t*-test to investigate the alteration of FC between before and after treatment for each treatment schedule. Finally, Pearson correlation analysis will be performed between the change in VAS score and the changes of FC in significant regions for three treatment schedules, respectively. The statistical analysis for the VBM will follow a similar procedure to that for the FC of PAG.

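### The link between connectivity change and pain change is tested arm by arm with no test between arms, so a correlation significant only in the CAT arm would not show a CAT-specific link

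*Protocol article*

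**What the plan says.** The last inferential step under Neuroimaging data analysis is that "Pearson correlation analysis will be performed between the change in VAS score and the changes of FC in significant regions for three treatment schedules". The closing word of that sentence says this is done for each schedule in turn, which makes it one correlation per arm and region. The number of regions depends on the earlier tests and is not fixed. The same section says the VBM statistics will follow a similar procedure, so the step appears to apply there too.

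The section names family-wise error correction for the VBM group comparison, for the baseline comparison with healthy controls and for the Time x Treatment mixed ANOVA on PAG connectivity. It names neither a correction nor a threshold for the correlations. The only level that reaches them is 0.05, from the general sentence under Clinical data analysis that begins "All hypothesis tests will be two-tailed analyses, with statistical significance determined by a".

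On numbers, Sample size calculation aims for 30 evaluable patients per arm. It then allows for dropout: "with an estimated loss rate of 8%, we will aim for 32 cases per group, resulting in a total of 96 cases". Allocation is "in a 1:1:1 allocation ratio". The connectivity analysis set is limited to completers: "The seed-based FC analysis will include all MWoA and HC participants and who completed the entire trial". Head motion can reduce it further, since only "images of participants with translations of less than 1 mm and rotational movements of less than 2° will be involved in the subsequent analysis".

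**The concern.** The mechanistic aim at the end of the Introduction, repeated in the Conclusion, is comparative: how CAT modulates the migraine network relative to IAT and sham CAT. The correlation is the only planned step that joins imaging change to pain change, and it gives three separate p-values with no comparison among them. Significance in one arm and not in another does not show that the two associations differ. With about 29 patients per arm, the significance pattern can vary between arms by sampling error alone. If the correlations came out significant only under CAT, the comparative aim would invite a claim that the analysis cannot carry. The primary VAS outcome is not affected.

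**Working it through.** **Patients per arm.** The plan aims for 30 evaluable patients, 8% loss and 32 randomised per arm. 30 x 1.08 = 32.4, rounded to 32, and 3 x 32 = 96, so the stated total is reproduced. (30 / 0.92 = 32.6 would round up to 33, which is immaterial here.) Evaluable: 32 x 0.92 = 29.4 per arm. I use n = 29. The head-motion rule could lower this, but no rate is given.

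**Assumptions.** The article gives no expected correlation and no number of regions. I take the same true r in all three arms, two-sided 0.05, and regions treated as independent.

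**Threshold.** At n = 29, |r| must exceed 0.367 for p < 0.05.

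**Chance of a CAT-only result.** With p the power in one arm, P(CAT only) = p(1 - p)^2 for one region, and 1 - [1 - p(1 - p)^2]^k for at least one of k regions. Power is from simulation, 200,000 samples per setting (r = 0: p set to 0.05).

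| True r, equal in all arms | Power per arm | CAT only, 1 region | At least one of 3 regions | At least one of 5 regions |
|---|---|---|---|---|
| 0 | 5.0% | 4.5% | 12.9% | 20.6% |
| 0.2 | 18.0% | 12.1% | 32.1% | 47.5% |
| 0.3 | 35.9% | 14.7% | 38.0% | 55.0% |
| 0.4 | 59.2% | 9.8% | 26.7% | 40.4% |
| 0.5 | 81.3% | 2.8% | 8.3% | 13.4% |

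The single-region figure cannot exceed 4/27 = 14.8%, reached at p = 1/3. With n = 30 or 32 it moves by less than 2 percentage points.

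**False positives.** With no association, one region tested in three arms gives 1 - 0.95^3 = 14.3% for at least one significant result.

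**What a direct comparison could detect.** For two arms of 29, Fisher z has standard error sqrt(2/26) = 0.277. An observed correlation of tanh(1.96 x 0.277) = 0.50 against 0 is needed for significance. Power is Phi([atanh(r1) - atanh(r2)] / 0.277 - 1.96):

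- 0.4 against 0: 33%
- 0.5 against 0: 51%
- 0.6 against 0: 70%
- 0.5 against 0.2: 24%

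For 80% power the contrast must be about tanh(2.80 x 0.277) = 0.65 against 0.

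**What pooling gains.** The correlation detectable with 80% power is tanh(2.80 / sqrt(n - 3)). For one arm, n = 29, it is tanh(2.80 / 5.10) = 0.50. For three arms, n = 3 x 29 = 87, it is tanh(2.80 / 9.17) = 0.30.

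**The case against.** The strongest reply is that the protocol does compare the arms directly. The Time x Treatment ANOVA with family-wise error correction tests whether connectivity change differs among CAT, IAT and sham CAT, and the correlations are only a follow-up in regions already found significant. This is right as far as it goes, and the comparative claim about connectivity itself can rest on the ANOVA. But the ANOVA concerns mean FC change. It does not test whether FC change tracks pain relief, or whether that link differs by arm.

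A reader might infer that the whole mechanistic conclusion will rest on comparing p-values between small arms. The article does not say so. Neither Anticipated results nor the Conclusion ties its mechanism claim to a correlation found only under CAT.

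A reader might also infer that a CAT-only pattern will often arise by chance. For a single region that is too strong: it is at most 14.8%, 4.5% with no association and about 3% at r = 0.5. The higher rates need several regions and moderate r. All regions share one PAG seed and, within an arm, the same VAS changes, so independence is doubtful. Positive dependence would pull the multi-region figures down towards the single-region ones. The chance that the three arms disagree in any way is larger (69% at r = 0.3, 72% at r = 0.4). It also counts patterns such as IAT only or CAT plus IAT, so it does not measure this problem.

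Finally, the 0.05 level comes from the clinical section, and a condensed article may leave correction of a follow-up step to an analysis plan that is not shown. The multiplicity limb is therefore the weaker one. The arm-by-arm form of the test is stated outright, and that limb stands.

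**Conclusion.** The point holds as a weakness in the mechanistic analysis that should be corrected. As written, the correlation step cannot show that a brain-symptom link is specific to CAT, whatever pattern of p-values appears. This conclusion is logical and needs no assumed effect size. How often a misleading CAT-only pattern would occur does depend on assumptions: about 3% to 15% per region for equal r of 0 to 0.5 at n = 29, and about 27% to 55% for 3 to 5 independent regions at r of 0.2 to 0.4. The documents do not support the stronger readings, that such a pattern is frequent in any one region or that the authors intend to base their conclusion on it.

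**What to change.** For each significant region, fit one model across the three arms: VAS change on FC change, arm and arm x FC change, adjusted for baseline VAS and baseline FC. Both baselines are already collected. Adjustment matters because each change score depends on its own baseline. Test the pooled slope and the interaction, with Holm or FDR correction over regions. Report per-arm correlations with confidence intervals as descriptive. Apply the same to VBM. State in advance that a CAT-specific link will be claimed only on the interaction.

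This changes the analysis text and needs no new data. There are two costs. Fewer correlations will be nominally significant. The interaction will also have low power (the two-arm figures above are a guide: 33% for 0.4 against 0, 51% for 0.5 against 0), so a non-significant interaction must not be read as equal associations. In return, the pooled slope on about 87 patients detects r of about 0.30 with 80% power, against about 0.50 within one arm.

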### Anticipated results

Periaqueductal gray plays a bi-directional role in both upward and downward projections, and is involved in the regulation of several analgesic pathways, including four main ones (see Figure 4): (1) The brainstem downward inhibitory system, i.e., the anterior cingulate cortex (ACC)-PAG-rostral ventral medulla (RVM)-spinal cord dorsal horn (SCDH)/spinal tract nucleus of the trigeminal nerve (STNT) pathway (Heinricher et al., 2009; Kong et al., 2010).(2) Midbrain limbic analgesic circuit, i.e., nucleus accumben (Acb)-amygdala (Amy)-habenular nucleus (Hb)-PAG-RVM (Napadow et al., 2007; Fang et al., 2009); (3) arcuate nucleus (ARC)-nucleus raphe medius (NRM)-locus coeruleus (LC) – PAG – SCDH pathway (Longchuan et al., 1988); and (4) Thalamic nucleus submedius (Sm)-Ventrolateral orbital cortex (VLO)-PAG-spinal cord loop (Jingshi and Bin, 2002). The results of this study will elucidate the central mechanism of contralateral acupuncture for migraine, whereby analgesic messages from CAT may be delivered simultaneously through one or more analgesic pathways of PAG transmission.

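### The imaging plan names no contrast that decides the mechanism aim and repeats the connectivity tests for grey matter, unranked, at a separate 0.05: false-positive rate about 9–10%, up to about 28%

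*Protocol article*

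**What the plan says.** The Introduction defines the second aim as a comparison of CAT's effect on the migraine network with that of sham CAT and of IAT. The Abstract and Introduction single out PAG connectivity, and Seed-based FC analysis fixes the seed's coordinates and radius.

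Neuroimaging data analysis in the Protocol article then lists, for connectivity:

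- a baseline comparison: "the FC of PAG in the baseline session will be compared between the migraine patients and normal participants";
- a "two-factor three-level mixed design ANOVA (Time: baseline and after treatment; Treatment: CAT, IAT, and sham CAT"), run "to explore the effect of treatment schedule on the FC of PAG after FWE correction";
- paired t-tests, labelled post hoc, of before against after within each arm;
- correlations of connectivity change with VAS change, arm by arm, in regions already significant.

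Grey-matter volume (VBM) comes in at the end: "The statistical analysis for the VBM will follow a similar procedure to that for the FC of PAG". Earlier in the same section VBM is also given a covariate-adjusted two-sample t-test between groups. The threshold there is: "A significant difference between groups will be indicated when *p* < 0.05 (FWE corrected").

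Anticipated results says the study will clarify the central mechanism, and that "analgesic messages from CAT may be delivered simultaneously through one or more analgesic pathways of PAG transmission". The Conclusion promises evidence of high quality on the mechanism.

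**The concern.** Correction for family-wise error (FWE) across voxels protects one map. It does not protect a claim that several maps, or two modalities, could each support. As written, a null connectivity result could be followed by a chance grey-matter result, and the report could still present a mechanism found at a corrected 0.05.

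The tests also do not match the aim. The aim is about differences between arms, but the only connectivity follow-up is change within each arm. A significant change under CAT does not show that CAT differs from sham, because any change common to all arms would appear there too. A significant three-arm interaction could come from IAT differing from sham, with CAT playing no part. A reader cannot tell beforehand which result would confirm the hypothesis and which would refute it.

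This bears on the trial's main message: imaging is the sole basis for the sample size, and the closing sections state the mechanistic conclusion firmly.

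**Working it through.** **Inputs from the Protocol article.** Level per map: 0.05, FWE-corrected (Neuroimaging data analysis). Two-sided testing is stated only under Clinical data analysis: "All hypothesis tests will be two-tailed analyses, with statistical significance determined by a *p*-value < 0.05". Modalities: 2. Within-arm paired tests: 3 per modality. Evaluable patients per arm: 30 (Sample size calculation).

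**Assumptions not in the document.** Correlation between modalities 0 to 0.5. Each map is treated as one test with error exactly 0.05.

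**The plan's own figures.** It states no error rate across maps, so there is none to reproduce. Its sample size of 32 per arm is 30 allowing for 8% loss: 30 × 1.08 = 32.4 and 30/0.92 = 32.6, so 32 is reproduced to within one patient. That calculation uses no significance level and is not affected here.

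**Formula.** With k independent maps at 0.05 and no true effect, P(at least one significant) = 1 − 0.95^k.

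1. Connectivity interaction alone, k = 1: 5%.
2. Interaction in both modalities, k = 2: 1 − 0.95² = 9.75%. For two correlated two-sided normal tests the rate is 9.6% at correlation 0.2 and 9.1% at 0.5. If the paired tests are run only after a significant interaction, they cannot add a false positive when nothing is true, so this row still applies.
3. Interaction plus the CAT arm's paired test, both modalities, k = 4: 1 − 0.95⁴ = 18.5% if independent.
4. Interaction plus all three paired tests, ungated, both modalities, k = 8: 1 − 0.95⁸ = 33.7% if independent.

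**Dependence in row 4.** The paired tests use the same change scores as the interaction, so independence overstates the rate. A simulation of 20,000 null trials with 30 per arm, one summary measure per modality, and a significant interaction or any significant paired test counted as a hit, gave 15.0% for one modality. For two independent modalities: 1 − (1 − 0.14975)² = 27.7%.

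**Reading.** The rate depends on what is allowed to support the claim: 5% (row 1), 9.1–9.75% (row 2), and up to about 28% (row 4 with dependence kept). The 15.0% shows that ranking VBM lower is not enough by itself; the status of the paired tests must also be settled.

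**The case against.** The best defence is that the protocol already leans towards one analysis. PAG connectivity is the stated core hypothesis, the seed is fixed, and the ordered sequence is written for connectivity, with VBM added in one sentence. The ANOVA is described as exploring, the paired tests are called post hoc, and the correlations are confined to significant regions. The only designated primary outcome is clinical. A fuller analysis plan, not shown, may set the hierarchy. Much of this stands: it is wrong to say that nothing is labelled exploratory or that connectivity is given no emphasis, and if the claim rests on the connectivity interaction alone the rate is 5%. What remains is that the article itself fixes the tests, the threshold and the parallel VBM sequence, chooses within-arm follow-up for a between-arm aim, and pairs exploratory wording with firm conclusions.

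Three stronger readings are tempting and not supported.

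- A reader might count seven maps per modality (baseline, three ANOVA effects, three paired tests) and infer an error rate above 50%. All 14 maps do give 1 − 0.95¹⁴ = 51.2%, but only if all are independent and ungated and each can confirm a CAT mechanism. Pre-treatment patient-control maps cannot show what CAT does, and neither the Time nor the Treatment main effect isolates a CAT-specific change. At correlation 0.5 the 14 maps give 34.8%.
- A reader might take the wording about one or more pathways as a further source of inflation. Whole-brain FWE already covers a hit anywhere in a map, and a grey-matter cluster is not by itself a PAG pathway.
- A reader might infer further tests from "The MRI data will be analyzed using PANDA, GRETNA and BrainNet Viewer toolboxes and SurfStat". That sentence names software; it states no additional hypothesis test.

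**Conclusion.** The point holds in limited form. PAG connectivity is the core hypothesis, but no effect or arm contrast is named to decide the second aim, the connectivity follow-up is within-arm only, and VBM repeats the sequence at 0.05 without a rank. If either modality may carry the mechanism claim, its false-positive rate is nearly double the nominal 5%. The upper figure of about 28% needs two further conditions: that the paired tests are not gated on the interaction, and that a change in any arm is read as support. The article excludes neither, but the post hoc label makes gating a reasonable reading.

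All figures assume no true effect and exact control within each map. Seed-based FC analysis says only that a clusterwise correction will be considered. If it were not applied, the rates would be higher by an amount the document does not allow one to compute.

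**What to change.** In Neuroimaging data analysis:

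- Name the Time x Treatment effect on PAG-seed connectivity, FWE-corrected at 0.05, as the primary imaging test.
- Only if it is significant, test the between-arm contrasts of change, CAT versus sham CAT and CAT versus IAT. These are needed because the three-arm effect alone could be driven by IAT versus sham.
- State that within-arm paired tests are descriptive.
- State that VBM and any other network analysis are supportive or exploratory, or are tested only after a significant connectivity result.

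The wording in Anticipated results and the Conclusion should then follow that order.

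This returns the mechanism claim to a 5% error rate and needs no extra patients, scans or procedures. The cost is that a VBM or within-arm finding alone can no longer carry the mechanism claim. If the sponsor wants VBM to be able to do so, the alternative is to split the level, 0.025 for each modality's interaction test, which holds the pair to at most 5% at some loss of power for connectivity.

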### Safety assessments

During the baseline period, all participants will undergo routine blood, urine, and stool tests, as well as electrocardiograms. Adverse events (AEs) encompass those related to acupuncture treatment, such as bleeding, hematoma, pain, and syncope, as well as symptoms potentially resulting from drug use, including headache, nausea, and vomiting. These incidents will be meticulously documented on the CRFs when they occur. In cases of serious adverse events, such as death, life-threatening disability, or hospitalization, the study leader will promptly report these occurrences to both the site and the hospital’s ethics committee within 24 h and ensure their accurate inclusion in the CRF. All AEs will be diligently followed up until they are appropriately addressed. Decisions regarding the potential termination of the trial will be made by the research ethics committee if deemed necessary.

